**Conclusions::**

There are currently no mHealth dietary interventions that specifically focus on increasing fiber intake in Japan, highlighting the novelty of this intervention. This trial will generate important evidence on the efficacy, feasibility, and safety of an AI-based mHealth intervention for enhancing dietary fiber intake and glycemic control in free-living individuals with T2D. Furthermore, as a pilot study, it will offer valuable insights into the development of AI as a promising tool for accurate, low-burden dietary assessment.

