#### Official Study Enrollment and Randomization

Randomization will be conducted using a dynamic allocation method based on minimization, with an allocation ratio of 1:1. The allocation adjustment factors will include the baseline dietary fiber intake during run-in (under 10 g, 10 g and above), sex (male and female), and HbA_1c_ level on the date of consent (less than 8.5% and 8.5% or higher). Random allocation will be performed online using the INDICE cloud system provided by the University Hospital Medical Information Network (UMIN). After randomization, a CRC will explain the details of the intervention according to the study participants’ allocated group (intervention or control). Participants are blind to their group.

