### Statistical Analysis Plan

In this study, we define 3 analysis populations: the full analysis set (FAS), the per protocol set (PPS), and the safety analysis set (SAS). The FAS is defined by all the study participants who had at least one primary outcome or secondary outcome obtained after randomization. We will follow the intention-to-treat (ITT) principle and analyze data based on the assigned group in the FAS analysis. The PPS is the FAS population with exclusion of patients who were found to have serious violations of the provisions of the research protocol:

Violation of inclusion and exclusion criteriaStudy participants who log fewer than 2 meals per day on more than 7 days within any of the following 2-week intervals during the intervention period: Weeks 1‐2, 3‐4, 5‐6, 7‐8, 9‐10, 11‐12, or 13‐14.In the event of a medical condition that makes dietary fiber intake inappropriate for the study participants,

Major deviations from other provisions of the study protocol will be assessed through a blinded review process. The blinded review will be conducted according to the following procedures: assessment of whether individual participants or specific measurement data should be excluded from the PPS or FAS; evaluation of participants with significant protocol deviations to determine whether exclusion is warranted; and examination of efficacy outcomes, including consideration of potential variable transformations and identification of outliers.

The safety analysis set is the set of all patients who used either MealLog or FiberMore at least once after randomization. In the safety analysis using the SAS, we will analyze data based on the intervention actually used by patients regardless of allocation. The FAS will be the primary analysis population, and the PPS will provide supportive results. All safety analyses will be conducted in the SAS. Data on patients’ characteristics will be presented as mean, minimum, SD, 25th percentile, median, 75th percentile, and maximum for continuous variables and as frequency and proportion for categorical variables.

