### Primary Outcome Analysis

We will perform analysis of covariance on the change in dietary fiber intake from the time of run-in to the end of the intervention period, with dietary fiber intake from the time of run-in as the covariate. The change in dietary fiber from the time of run-in and at the end of the intervention period will be calculated as ([average dietary fiber over week 11 and 12]-[average baseline dietary fiber during the run-in]). The estimated mean change in each group and its 2-sided 95% CI will be calculated. Additionally, the estimated difference between groups and its 2-sided 95% CI will be calculated.

To ensure reliable estimates of fiber intake, days with only 0 or 1 logged meal will be excluded from the analysis.

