We will also calculate the percentage of responses for each option on the Likert scale and for the “Yes or No” scale in “Survey on participants’ satisfaction and perceived usefulness of the intervention” at the end of the intervention period for both intervention group and control group. For the “Survey on intention to improve eating habits using a Generative AI-enabled app”, we will calculate the percentage of responses for each option on the Likert scale at the end of the observation period for the intervention group.

As part of our exploratory analysis, we will assess the reliability of the TPB questionnaire using the Cronbach α coefficient. Additionally, we will conduct multivariate regression analyses to examine various associations related to the TPB constructs. Specifically, we will investigate the relationship between changes in intention (INT) to increase fiber intake and changes in fiber intake outcomes both between and within groups. Furthermore, we will analyze the associations between changes in attitude (ATT), subjective norms (SN), and PBC with changes in intention to increase fiber intake, as well as the relationship between changes in PBC and changes in fiber intake outcomes at both the between-group and within-group levels. The impact of the intervention on INT via ATT, SN, and PBC will be evaluated through mediation analysis.

We will calculate the frequency and weekly percentages of the following measurements during the intervention period in the intervention: number and percentage of days fiber goal is met out of 7 days, the number and percentage of implemented solutions in a week, the average weekly fiber change in the intervention group from run-in, and the average weekly energy change in the intervention group from run-in. We will also evaluate the effects of changes in dietary fiber intake on changes in BMI and HbA_1c_ using the Pearson correlation test and simple regression analysis.

We will perform a statistical analysis of safety outcomes by calculating the number and percentage of individuals who experience adverse events during run-in, intervention, and observation periods. During the intervention and observation periods, data will be compiled separately for the intervention and control group, and the percentages will be compared between groups using the Fisher exact test.

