## Results

Recruitment began on February 12, 2025, and ended on September 1, 2025. We anticipate the intervention period will conclude in December 2025 and the observation period will conclude in March 2026.

As of September 22, 2025, 4947 patients have been screened for eligibility and 81 participants have been recruited to the study. A total of 72 participants have been officially enrolled and randomized. Progress through the phases of this planned randomized trial (enrollment, intervention allocation, follow-up, and data analysis) will be visually represented using the CONSORT (Consolidated Standards of Reporting Trials) flow diagram (see Figure 6).

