We acknowledge that AI may misclassify food items and also portion sizes, which may introduce bias in the dietary estimates. These image recognition models are typically trained on datasets featuring popular or standardized foods, which may limit their ability to accurately classify ingredients in less common meals, such as regional specialties, traditional home-cooked dishes, or foods from rural areas. Nevertheless, the AI model used in this study has been fine-tuned using a dataset of real-world meal photos, resulting in improved accuracy in estimating dietary fiber content. Our fine-tuned AI model demonstrates better accuracy in estimating fiber and energy content from meal photos than dietitians, whose estimation capabilities are widely regarded as an acceptable standard for validating dietary intake [55]. Since our AI model exceeds expert-level accuracy in estimating dietary fiber and energy content from meal images, we believe that the model is sufficiently reliable for the purposes of this intervention.

This pilot RCT will provide important evidence on the efficacy, feasibility, and safety of an AI-based mHealth intervention in improving dietary fiber intake and glycemic control among free-living T2D patients. This pilot study offers valuable insights and evidence on the development of AI as a promising method for accurate, low-burden dietary assessment [37], including how participants engage with AI-based meal logging and respond to AI-driven diet intervention. Additionally, this study has the potential to generate a large volume of meal photos taken in real-world conditions, which can be leveraged for further fine-tuning and improving the AI model’s accuracy and performance in analyzing user-generated meal images.

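### Safety evidence is promised, but the only stated between-group safety comparison is a Fisher test at about 36 per arm; a risk difference with a 95% CI should be added

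*Protocol article*

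**What the plan says.** The promise appears twice. The abstract's Conclusions state: "This trial will generate important evidence on the efficacy, feasibility, and safety of an AI-based mHealth intervention". The closing paragraph of the Discussion repeats it: "This pilot RCT will provide important evidence on the efficacy, feasibility, and safety of an AI-based mHealth intervention".

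The safety method is in the Secondary Outcomes Analysis section. It consists of "calculating the number and percentage of individuals who experience adverse events during run-in, intervention, and observation periods". For the two periods after randomization the data are compiled by group, and "the percentages will be compared between groups using the Fisher exact test". No risk difference, ratio or interval is stated for adverse events.

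The Primary Outcome Analysis section, in contrast, says that for fiber intake "the estimated difference between groups and its 2-sided 95% CI will be calculated", and the HbA1c change is handled in the same way.

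The Statistical Analysis Plan section defines the population: "The safety analysis set is the set of all patients who used either MealLog or FiberMore at least once after randomization". On size, the Results section reports: "A total of 72 participants have been officially enrolled and randomized". Randomization was by minimization "with an allocation ratio of 1:1".

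**The concern.** A reader of a safety statement needs to know how large an excess of adverse events the data leave open. A test of no difference does not answer that. In a small trial a p-value above 0.05 is compatible with no excess and also with a large one.

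The question matters here because the Discussion itself expects that more fiber may cause gastrointestinal effects and describes design features meant to limit them. If the report gives arm percentages and a non-significant p-value under a heading of important safety evidence, readers could take more reassurance from it than about 36 patients per arm can give.

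**Working it through.** **Inputs from the article.** 72 randomized at 1:1, so 72 / 2 = 36 per arm if the split is even. Two-sided Fisher exact test; the 5% level is taken from the Sample Size Consideration section.

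**Inputs assumed.** Adverse-event rates. The article gives none, so a range is shown.

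**1. The plan's own sample size.** With a 7 g difference, SD 9.85 g, two-sided 5% and 80% power, the normal approximation is

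n = 2 × (1.960 + 0.842)² × 9.85² / 7² ≈ 31.1, rounded up to 32 per arm.

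The exact t-test calculation gives 32.07, rounded up to 33, which matches the stated 33 per group. The trial is therefore sized on fiber intake. No power or precision figure is stated for safety.

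**2. Power of the Fisher test at 36 per arm.** Power is the sum of Bin(x; 36, p_control) × Bin(y; 36, p_intervention) over all tables (x, y) with Fisher p ≤ 0.05.

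| Control | Intervention | Power |
|---|---|---|
| 5% | 10% | 3% |
| 10% | 20% | 14% |
| 15% | 30% | 24% |
| 20% | 40% | 37% |
| 25% | 50% | 50% |
| 30% | 60% | 64% |
| 40% | 80% | 91% |
| 30% | 50% | 31% |
| 40% | 60% | 29% |

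The first seven rows are doublings. A doubling is missed at least as often as it is found up to a control rate of about 25%, and is found more often than missed above that. At high control rates, however, a doubling is a very large absolute excess (30 points at a control rate of 30%). A 20-point excess over a control rate of 30% or 40% has only about 30% power.

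**3. What an interval would show.** Newcombe 95% CI for the difference d = p_I − p_C, where (l, u) are the Wilson limits in each arm:

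lower = d − √[(p_I − l_I)² + (u_C − p_C)²]

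upper = d + √[(u_I − p_I)² + (p_C − l_C)²]

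For 4 of 36 in each arm, p = 11.1% with Wilson limits 4.4% and 25.3%. The half-width is √(14.2² + 6.7²) ≈ 15.7 points.

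| Control vs intervention (of 36) | Fisher p | Difference (points) | 95% CI (points) |
|---|---|---|---|
| 4 vs 4 | 1.00 | 0 | −16 to +16 |
| 9 vs 9 | 1.00 | 0 | −20 to +20 |
| 12 vs 12 | 1.00 | 0 | −21 to +21 |
| 18 vs 18 | 1.00 | 0 | −22 to +22 |
| 4 vs 8 | 0.34 | +11 | −7 to +28 |
| 7 vs 14 | 0.12 | +19 | −2 to +38 |
| 4 vs 10 | 0.13 | +17 | −2 to +34 |
| 12 vs 20 | 0.10 | +22 | −1 to +42 |

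The first four rows share one p-value but leave open excesses from about 16 to 22 points. The p-value carries none of that information.

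**4. Sensitivity to arm size.** For 20% vs 40%, power is 32% at 33 per arm and 41% at 40 per arm. For 25% vs 50% it is 48% and 56%. The conclusion does not depend on exactly 36. The control arm's safety set could be smaller than 36, because membership requires app use after randomization and controls are asked to log meals only in weeks 11 and 12.

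**The case against.** Two stronger readings are tempting, and the article supports neither.

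- A reader might infer that the plan will treat a non-significant Fisher test as proof of safety. No section says so. The abstract and Discussion promise evidence on safety without tying it to the test result, so this is a foreseeable misreading and not a stated rule.
- A reader might infer that the test would usually miss a doubling of adverse events whatever the rate. That depends on a control rate the article does not give. Above about 25% the statement reverses, and such a rate cannot be excluded for any adverse event over a 12-week period.

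Other points in the plan's favour also stand. Arm counts and percentages are planned, so a reader could derive an interval. Fisher's test is valid for small binary samples. The article also uses it, with no stated interval, for HbA1c below 7% and for newly added medications, so safety is not singled out. The trial is labelled a pilot, adverse events are described under secondary outcomes, and secondary results are to be interpreted as exploratory. An interval may exist in the full protocol or analysis plan, which is not shown.

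These points reduce the weight of the concern but do not remove it. The article does state a between-group safety method, and that method does not give the quantity a safety statement needs. The caution about exploratory interpretation is not repeated where the safety evidence is promised.

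**Conclusion.** The point holds as an inexpensive improvement to a stated method; it is not an error in the plan. At about 36 per arm, a non-significant Fisher test could not by itself support a safety conclusion. Power is 14% for 10% vs 20%, 37% for 20% vs 40%, and about 30% for a 20-point excess over a control rate of 30% or 40%. Even equal arms would leave an excess of about 16 to 22 points open for control counts of 4 to 18 of 36. This rests on an even split of the 72 randomized and on assumed adverse-event rates. The interval widths depend on the rate less than the power figures do, so they are the firmer part of the argument.

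**What to change.** In the safety paragraph of the Secondary Outcomes Analysis section, add the difference in the percentage of participants with adverse events (intervention minus control) with a two-sided 95% CI by the Newcombe or score method, separately for the intervention and observation periods. The Fisher p-value can stay as a supplement, so the prespecified comparison is kept.

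In the abstract's Conclusions and the closing paragraph of the Discussion, describe the safety evidence as preliminary and bounded by the upper confidence limit, that is, by the excess the trial cannot rule out. A non-significant difference should not be cited alone as evidence of safety.

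The cost is one extra column in the safety table and a less favourable safety statement. No new data are needed.
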